## Abstract

**Background:**

Primary prevention trials have demonstrated that the traditional Mediterranean diet is associated with a reduction in cardiovascular mortality and morbidity. However, this benefit has not been proven for secondary prevention after an acute coronary syndrome (ACS). We hypothesized that a high-intensity Mediterranean diet intervention after an ACS decreases the vulnerability of atherosclerotic plaques by complex interactions between anti-inflammatory effects, microbiota changes and modulation of gene expression.

**Methods:**

The MEDIMACS project is an academically funded, prospective, randomized, controlled and mechanistic clinical trial designed to address the effects of an active randomized intervention with the Mediterranean diet on atherosclerotic plaque vulnerability, coronary endothelial dysfunction and other mechanistic endpoints. One hundred patients with ACS are randomized 1:1 to a monitored high-intensity Mediterranean diet intervention or to a standard-of-care arm. Adherence to diet is assessed in both arms using food frequency questionnaires and biomarkers of compliance. The primary endpoint is the change (from baseline to 12 months) in the thickness of the fibrous cap of a non-significant atherosclerotic plaque in a non-culprit vessel, as assessed by repeated optical coherence tomography intracoronary imaging. Indices of coronary vascular physiology and changes in gastrointestinal microbiota, immunological status and protein and metabolite profiles will be evaluated as secondary endpoints.

**Discussion:**

The results of this trial will address the key effects of dietary habits on atherosclerotic risk and will provide initial data on the complex interplay of immunological, microbiome-, proteome- and metabolome-related mechanisms by which non-pharmacological factors may impact the progression of coronary atherosclerosis after an ACS.

**Trial registration:**

ClinicalTrials.govNCT03842319. Registered on 13 May 2019

**Supplementary Information:**

The online version contains supplementary material available at 10.1186/s13063-021-05746-z.

## Background

Cardiovascular morbidity and mortality are mainly associated with atherosclerosis, a systemic, chronic, dynamic, progressive and incurable condition [1]. Atherosclerosis causes coronary artery disease (CAD), the most prevalent non-communicable disease in Western countries. The first manifestation of CAD is often an acute coronary syndrome (ACS), which is a life-threatening condition. The number of hospital admissions for ACS in European countries varies between 90 and 312 per 100,000 inhabitants per year [2]. Despite the use of reperfusion therapy and intensive post-cardiac event treatments, 12% of patients admitted due to an ACS will die within the following 6 months [3].

Atherosclerosis is initiated by endothelial dysfunction [4] followed by the accumulation of cholesterol into the subendothelium of large arteries, which triggers a response cascade that results in the promotion of plaque formation. Whenever the fibrous cap that separates the plaque from the vessel lumen is broken, the highly thrombogenic plaque material is exposed to the blood, locally triggering the intracoronary thrombosis phenomena responsible for ACSs. Immune-mediated complexes are key pathophysiological elements for plaque rupture [5, 6]. Vulnerable plaques at the highest risk of rupture have a large lipid core. But most importantly, the risk of plaque rupture is inversely proportional to the thickness of this fibrous layer [7]. By facilitating plaque rupture and promoting thrombogenicity, systemic inflammation is known to increase the risk of an ACS. Moreover, beyond these local factors, coronary plaque complications frequently associate a widespread inflammation of the full coronary arterial bed [8].

After an ACS, a complex process of lesion repair and vessel healing takes place. Inflammation plays a central pathophysiological role in vessel healing [9] and is also involved in the process of ischemia-reperfusion injury and myocardial healing of the ischemic myocardium. Closely related to inflammation, gut dysbiosis is also involved in the pathogenesis of atherosclerosis by a number of mechanisms [10]. The oral cavity is the inlet of the gastrointestinal and respiratory systems and is connected extensively to the blood stream via the highly vascularized oral mucosa [11]. In addition, oral microbiota may be a factor in the early phases of atherosclerosis due to its direct involvement in vascular function [12–14].

Consequently, after an ACS, the complex interplay between inflammation, changes in microbiota and gene expression is a potential target for dietary interventions. The Mediterranean diet (MedDiet), based on the traditional dietary pattern found in olive-growing areas [15, 16], is particularly well suited for this purpose. The traditional MedDiet reduces cardiovascular mortality [17, 18]. The Lyon randomized trial [19] and the large primary-prevention PREDIMED trial have demonstrated that a MedDiet intervention reduces the incidence of major cardiovascular events [20, 21]. Several molecular mechanisms seem to be involved in the risk-reduction effect of MedDiet in primary cardiovascular prevention [22–26]. Epidemiological evidence [27] and clinical trials [28] suggest that cardiovascular protection is achieved by consuming either extra-virgin olive oil (EVOO) or nuts, together with an emphasis in plant-derived foods—key elements of the MedDiet. Moreover, it improves endothelial function and reduces blood pressure compared to a low-fat diet [29]. MedDiet also contains nitrate-rich green leafy vegetables, which have been shown to improve cardiovascular parameters [30]. Although this evidence anticipates a potential beneficial effect of a high intense MedDiet intervention after an ACS, a comprehensive mechanistic understanding of how MedDiet influences cardiovascular risk and the atherosclerotic substrate is lacking. The effect of a MedDiet intervention on the microbiota and the immune system and its potential for secondary prevention also remains unknown. This information could be of great value not only to support clinical prescription of traditional MedDiet after an ACS, but also to shed light on the molecular pathways involved in the natural history of atherosclerosis and, eventually, to identify new targets for preventing disease progression.

## Methods/design

The MEDIMACS clinical trial is designed on the global hypothesis that a comprehensive view of the biological processes triggered by diet nutrients provides new insights into the roles of the immune response and microbiome-related metabolism on coronary artery disease progression, plaque stabilization and coronary physiology. To test this hypothesis, we use an experimental randomized clinical trial design. The alternative hypothesis is that, compared to standard of care, a high-intensity MedDiet intervention after an ACS increases the fibrous cap thickness of atherosclerotic plaques. Fibrous cap thickness has been demonstrated to be a major determinant of plaque vulnerability, and it is a sensitive surrogate of cardiac ischemic events in the long term [31].

The MEDIMACS study is a 1:1 prospective, randomized, controlled, mechanistic and multidisciplinary clinical trial designed to address the effects of a 12-month intensive dietary intervention based on the traditional MedDiet on atherosclerotic plaque vulnerability and coronary endothelial dysfunction. Researchers who will address the primary outcome are blinded to the intervention assignment. Patients are being recruited in a single tertiary hospital in Spain.

### Study objectives

The general aim of the MEDIMACS trial is to determine the immunological, microbiome-related, proteomic, metabolomic mechanisms by which the Mediterranean diet impacts the progression of coronary atherosclerosis in patients after an ACS. The principal objective of the clinical trial is to address the effect of the Mediterranean diet on coronary plaque vulnerability after an ACS. Secondary objectives are (1) to determine the role of MedDiet on microbiome-related inflammation, nitric oxide metabolism, oxidative stress, choline metabolism and lipid metabolism; (2) to define molecular pathways responsible for interplay between diet, microbiota and atherosclerotic plaque progression and stabilization through a personalized evaluation of the immune, proteomic and metabolomic profiles; (3) to propose candidate biomarkers for patient stratification and prediction of the diet response; and (4) to propose microbiome-targeted therapeutic strategies in secondary prevention after an ACS.

### Participants

Patients admitted at the Hospital General Universitario Gregorio Marañón, Madrid, for an ACS fulfilling inclusion criteria (Table 1) are prospectively enrolled in the study within the first 72 h after hospital admission.

**Table 1 Tab1:** Inclusion and exclusion criteria for the MEDIMACS clinical trial

Inclusion criteria	
1. Equal or older than 18 years	
2. An established diagnosis of ACS based on clinical, electrocardiographic and laboratory criteria	
3. An intermediate (20–60% lumen stenosis) atherosclerotic lesion identified in a non-culprit coronary artery with diameter > 2.0 mm (target lesion) not undergoing percutaneous coronary intervention at the time of the revascularization procedure	
4. Willingness to modify his/her diet	
5. Able to follow up and answer questionnaires	
Exclusion criteria	
1. Thrombolysis in Myocardial Infarction (TIMI) score < 3 in the culprit vessel (unsuccessful revascularization)	
2. Killip classification III/IV	
3. Active systemic infection, chronic inflammatory disease, periodontal disease or treatment with corticosteroids, antibiotics or immunomodulators within the past 3 months	
4. Renal insufficiency with glomerular filtration less than 30 mL/min	
5. Severe hepatic insufficiency (liver cirrhosis in Child B or C stages)	
6. Any comorbidity with life expectancy of less than 1 year	

Trial overview and allocation are shown in Fig. 1. Before undergoing coronary angiography (performed on clinical grounds), patients are informed by clinical cardiologists about the research project and invited to sign the informed consent document. Coronary intervention procedures are indicated. The MEDIMACS intracoronary research diagnostic study is initiated after completing the revascularization procedure of the culprit coronary lesion, when indicated. Only patients showing an intermediate lesion (20–60% of lumen area) in a non-culprit vessel are finally enrolled in the study (see the “Inclusion criteria” section). This intermediate lesion is labelled as the target lesion for the measurement of the primary endpoint. Within the following 12 h, patients are randomized to receive either a high-intensity intervention to promote the traditional MedDiet or standard-of-care recommendations for 12 months.

**Fig. 1 Fig1:**
[figure not shown]
The MEDIMACS trial overview

### Randomization

Patients will be 1:1 randomly allocated into two groups, intensive MedDiet intervention or standard of care. Randomization is conducted blindly by means of an Internet-based, computer-generated random-number system. The Department of Preventive Medicine and Public Health of the University of Navarra is responsible for the randomization procedure. Participants are stratified by sex and age (< 66, 66–75, > 76 years). The system automatically allocates each participant to their assigned group according to a random and non-predictive algorithm, out of control of any staff involved in the trial. To obtain approximately equally sized groups, the random generation system is adaptive, meaning that the probability of treatment assignment changes according to assigned treatments of patients already in the trial. This implies recalculation of treatment assignment probabilities for each new patient.

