### Statistical analysis plan

The primary endpoint will be analysed by intention to treat using a linear mixed-effects model accounting for repeated measures. Values of cap thickness will be entered as the dependent variable. The visit, the treatment group and their interaction will be entered as fixed effects, whereas the patient identification is entered as random effect. Thus, the coefficient of the term accounting for the interaction between the treatment group and visit provides an adjusted estimate of the magnitude of change in thickness at 1 year attributable to the effect of the intervention. The 95% confidence interval of this estimate will be assessed by asymptotic and bootstrap methods. Under a missing at random assumption, this method gives unbiased estimates of the effect. Quantitative indices of endothelial function, coronary physiology and additional metrics of plaque composition will be also analysed using linear mixed-effects models. The analysis of clinical outcomes will be conducted using the Kaplan-Meier method and the log-rank test to compare both intervention groups. Statistical comparisons will be 2-tailed and a statistical significance level of 0.05 shall be considered. Uni- and multivariate linear and non-linear mixed and regression models, adjusting for covariables, will be conducted for the relationship of microbiota composition (diversity and abundance metrics), the number and type of immune cell populations, proteins and metabolites and diet and clinical outcomes.

A modified intention-to-treat analysis including all randomized patients who undergo the catheterization procedure at a 12-month follow-up visit will be used to evaluate the primary endpoint and all secondary endpoints (*intention-to-treat analysis set*). In addition, a per-protocol analysis will be performed following recent directions for analyses of pragmatic trials to control for confounding [42] after excluding from the intervention arm those patients in whom the food frequency questionnaires and biological markers indicate low compliance to the prescribed MedDiet (*per-protocol set*). Secondary endpoints #4–10 will be analysed in all patients that complete the 12-month follow-up period regardless if they undergo the follow-up catheterization procedure or not (*full analysis set*).

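### Allocation is stratified by sex and age but the primary model uses neither, which costs some precision if they predict the change in cap thickness; the printed age bands also omit age 76

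*Protocol article*

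**What the plan says.** Randomization section: "Patients will be 1:1 randomly allocated into two groups, intensive MedDiet intervention or standard of care". The factors and bands are given as "Participants are stratified by sex and age (< 66, 66–75, > 76 years"). The system is adaptive: "the probability of treatment assignment changes according to assigned treatments of patients already in the trial".

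Inclusion criteria (Table 1): "Equal or older than 18 years", with no upper age limit.

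Statistical analysis plan section, primary endpoint: "The visit, the treatment group and their interaction will be entered as fixed effects, whereas the patient identification is entered as random effect". The treatment effect is read from one term: "the coefficient of the term accounting for the interaction between the treatment group and visit provides an adjusted estimate of the magnitude of change". On precision: "The 95% confidence interval of this estimate will be assessed by asymptotic and bootstrap methods".

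That section mentions adjustment for covariables only later, for the models relating microbiota, immune cells, proteins and metabolites to diet and clinical outcomes. It does not attach to the primary endpoint. The word 'adjusted' in the description of the interaction coefficient introduces no covariate, because none is listed.

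**The concern.** When allocation is balanced on a factor, that factor's chance contribution to the difference between arms is removed by design. An analysis that leaves the factor out still counts its variance as error. If the factor predicts the outcome being compared, the reported standard error exceeds the true sampling error, the confidence interval is too wide and the test rejects less often than its nominal level. The trial then gives up part of the precision its stratification provided. A simple patient-level bootstrap that ignores the strata would not correct this.

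The age bands raise a smaller, separate matter. The middle band ends at 75 and the top band starts above 76, so an eligible 76-year-old belongs to no printed stratum. Anyone building an age-stratum variable from the text would not know where to put those patients.

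**Working it through.** **Inputs.** From the Sample size section: effect 40% in relative change, SD 58%, two-sided alpha 0.05, power 0.80, 35 per group, 10% attrition, 100 randomised. From the Limitations section: 45% attrition. R², the share of variance in *change* explained by sex and age, is not in the article. It is assumed here over 0 to 0.20.

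**1. The plan's own figure.** n per group = 2 × [(1.960 + 0.842) × 58/40]² = 33.0; the t-distribution solution is 33.99, so 34. The article states 35, close enough to confirm that 40 and 58 are the working inputs.

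**2. Which terms can matter.** The effect is the group-by-visit interaction over two visits, in patients who have the 12-month catheterisation. With both visits present it equals the difference between arms in mean within-patient change. Sex or age differences in the *level* of cap thickness cancel in that change, so only factor-by-visit terms can alter the contrast. A simulation checked this with 90 completers, allocation balanced within sex-by-age strata, an assumed sex and age mix, and 150 runs per scenario:

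| Scenario | SE, no factors | SE, main effects only | SE, factor-by-visit |
|---|---|---|---|
| Factors predict level only (R² of change 0) | 8.93 | 8.93 | 8.95 |
| Factors predict change (R² about 0.18) | 9.9 | 9.9 | 8.9 |

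Adding main effects alone changed the estimate by about 10⁻¹³ and the standard error by less than 0.0003. With so few runs the simulated rejection rates are noisy, so they are not used.

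**3. Standard error and power.** The unadjusted SE is 58 × √(1/n₁ + 1/n₂). Adjustment multiplies the SD by √(1 − R²), so the unadjusted SE is too large by the factor 1/√(1 − R²). With 45% attrition, 55 patients remain (27 and 28): SE = 58 × √(1/27 + 1/28) = 15.64. With 10% attrition, 45 per arm remain: SE = 58 × √(2/45) = 12.23.

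| R² of change | Excess SE | Adjusted SE, 45 per arm | Power, 27 and 28 | Power, 45 per arm |
|---|---|---|---|---|
| 0 | 0% | 12.23 | 70.9% | 90.5% |
| 0.02 | 1.0% | 12.10 | 71.8% | 91.1% |
| 0.05 | 2.6% | 11.92 | 73.1% | 91.9% |
| 0.10 | 5.4% | 11.60 | 75.4% | 93.2% |
| 0.20 | 11.8% | 10.94 | 80.1% | 95.5% |

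The 27-and-28 column uses the noncentral t distribution with 53 degrees of freedom. Charging 3 more leaves 75.3% and 80.1% at R² 0.10 and 0.20, and 70.8% at R² 0. The 45-per-arm column uses the normal approximation; the t distribution gives 89.9% instead of 90.5% in the first row. Table 2 of the article prints 99.60% for the 40% effect. That matches 90 per arm (99.62%), not 45, and is a separate matter.

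**4. True size of the unadjusted 5% test.** With exact balance in the analysed patients, the true variance is (1 − R²) of the nominal variance. Size is then 2 × [1 − Φ(1.96/√(1 − R²))] = 3.9% at R² 0.10 and 2.8% at R² 0.20. Balance is created at randomisation, however. If a random 55% of patients are retained, 45% of the factors' variance contribution returns: (1 − R²) + 0.45R² = 1 − 0.55R². Then:
- R² 0.10: 2 × [1 − Φ(1.96/√0.945)] = 4.4%
- R² 0.20: 2 × [1 − Φ(1.96/√0.890)] = 3.8%

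A simulation of 100 patients in six strata (assumed mix, balanced within stratum, 55 kept at random, 20,000 runs) gave 4.3% and 4.0%, and 5.0% at R² 0.02.

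**5. Age bands.** Below 66, 66 to 75 and above 76 cover every whole-year age from 18 upwards except 76.

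**The case against.** The strongest reply is that the loss is hypothetical. The contrast is a within-patient change, level differences by sex and age are already removed, and nothing in the article says that either factor predicts change. This stands. A reader might infer that the primary confidence interval *is* too wide. The article supports only that it would be if R² of change exceeds zero, and at R² 0.02 the excess is 1%.

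A reader might also take 3.9% and 2.8% as the true test sizes. Those need exact balance among analysed patients. The article describes an adaptive algorithm aiming at approximately equal groups, and the analysis set is only those who return for catheterisation. Under random 45% loss, 4.4% and 3.8% are the better figures.

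The error is in the safe direction. Nothing suggests a biased estimate or an inflated type I error. Covariate terms are often settled in an analysis plan, and none is shown here. But the article spells the primary model out term by term, so this is a stated choice rather than an omission by condensation.

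On age 76, a reader might infer that such patients were not allocated or would drop out of the primary analysis. Neither follows. An automated system made every allocation, and the planned primary model has no stratum term from which they could be lost. The slip would matter only once age strata enter an analysis.

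**Conclusion.** The mismatch between design and primary model is certain as text; its cost is conditional. The unadjusted standard error exceeds the adjusted one by 0 to 11.8% for R² of change from 0 to 0.20, and the test is at most mildly conservative. The power gain from adjustment matters more if only 55 patients are evaluable (about 71% to 75% or 80%) than with 45 per arm (about 90.5% to 93% or 95.5%).

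These figures rest on an assumed R², on the 58% SD of relative change being a fair guide for a model fitted to thickness values, and on loss being unrelated to sex and age. The unadjusted powers also treat sampling variance as equal to model variance. Allowing for partial balance would raise them slightly and shrink the gain. This is an efficiency improvement at almost no cost, not a threat to validity. The gap at age 76 is a small wording error to be corrected alongside it.

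**What to change.** Before unblinded analysis, add sex-by-visit and age-by-visit terms, with their main effects, to the primary mixed model. If an ANCOVA is used instead, enter sex and age as covariates. Main effects alone in the mixed model would change nothing.

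Fix one form of age in advance, for example continuous age or the strata as the randomisation system coded them. Do not leave the choice to how sparse the oldest band turns out to be.

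Correct the printed age bands so that age 76 falls in the stratum the system actually used. Recruitment is complete, so this means reporting the coding, not altering any allocation.

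The cost is a few lines of text and about 3 degrees of freedom (one for sex, two for three age bands), out of 53 with 55 evaluable patients. If sex and age turn out not to predict change, the price at that sample size is about 0.1 percentage point of power (70.9% to 70.8%).

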### Diet intervention

#### Intervention group

Patients allocated to the high-intensity MedDiet intervention group (Fig. 1) are individually interviewed by a dedicated dietitian and participate in individual and group sessions at enrolment and at 3, 6, 9 and 12 months. A personalized MedDiet with detailed nutritional composition and total energy intake is adapted to participant’s weight, age and requirements and the dietitian advice for his/her individual needs. The high-intensity MedDiet indications promote the consumption of olive oil, fresh fruits, vegetables, nuts, legumes and fish. A detailed list of indications is specified in Additional file 1. Patients in this group are provided with 4 l per month of free EVOO during the 12-month follow-up period and undergo monthly phone-call follow-up interviews. Recipes, shopping lists and weekly menus are provided to optimize adherence to the traditional MedDiet, replicating the PREDIMED clinical trial [32].

